## Methods/Design

### Study design

This is a randomized controlled trial (RCT). In total, 120 novice runners will be recruited. Subjects will be randomly assigned to one of three groups: an isolated ankle strengthening group (n = 40), a functional balance training group (n = 40) or an activity matched control group (n = 40). The study design and flow can be seen in Figure 1. Research ethics approval was obtained from the University of Calgary’s Conjoint Health Research Ethics Board (Ethics ID: REB13-0153).

**Figure 1 Fig1:**
[figure not shown]
**Study design protocol.**

### Target population

The target population for this research project is novice recreational runners. Novice runners have been chosen for this study as they may be the most malleable for training effects. They have also been shown to have a higher incidence or running-related injuries than experienced runners[51–54]. A novice recreational runner will be identified as an individual with less than one year of running experience that runs at least twice a week for a total weekly distance greater than 5 kilometers as their main physical activity[54]. An age range of 18 – 60 years of age will be used for subject inclusion criteria. Inclusion criteria include the lack of any neurological abnormalities or any lower extremity injury or pain within the three months prior to testing and subjects should not have extensive prior experience with isolated joint strength training functional balance training within the last year.

### Sample size

Exploratory power analyses were completed for multiple biomechanical variables that will be tested in this study. Sample size was determined based on a sample size calculation using previously published data on the effects of balance training on the 95% ellipse area of the center of pressure as this was the largest reasonable sample size needed for the variables in this study[37]. It was found that in order to achieve 80% statistical power with an α = 0.05, 32 subjects would be needed to detect a change between training group and the control group with respect to the change in the 95% ellipse area following training with an effect size of 0.71. Assuming a 20% drop out rate, 40 subjects will be recruited for each of the groups in this project. Due to the sample size, the injury portion of this study will be a pilot RCT for developing a running injury prevention program. The information found in this study regarding the incidence of injury in each group will be critical for developing future RCTs investigating the impact of these interventions on running injury prevention.

### Randomization procedure

In order to protect against selection bias, subjects will be randomly assigned to one of the three groups. The generation of an unpredictable randomized allocation sequence will be completed using randomization.com through the use of a random allocation scheme (one block, size 120) with a 1:1:1 allocation ratio between the three groups. This randomization procedure was chosen to avoid selection bias with predictable random assignments using smaller block sizes in a non-blinded study design. This task will be completed by an individual that is not involved in the trial. In order to ensure allocation concealment, sequentially numbered, opaque, sealed envelopes (SNOSE) will be used. Once potential subjects have provided written, informed consent, they will sequentially draw an envelope and write their details on that envelope before opening to determine their group allocation. All envelopes will be similar in appearance and weight and cardboard will be placed within the envelope in order to make it impermeable to light.

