#### Measurements

Baseline characteristics will be collected for each subject including height, mass, running frequency, running experience, and injury history. Subjects will attend one testing session prior to the training intervention and one testing session immediately following the training intervention (within 9 weeks from baseline) for biomechanical data collection. These testing sessions will involve the collection of isokinetic strength data and the collection of lower extremity running mechanics (kinematics and kinetics) and postural control (dependent variables). Postural control will be assessed as balance deficits have previously been shown to be predictive of future ankle sprains in healthy athletes[57–59].

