### Isokinetic strength

As running is dynamic, isokinetic measurements of strength will be completed. Isokinetic strength will be measured using a Biodex System 3 dynamometer (Biodex Medical System Inc, New York, NY, USA) to assess average peak torque for ankle eversion/inversion strength, ankle plantar flexion/dorsiflexion strength, knee flexion/extension strength and hip ab/adduction strength. For each movement, three maximal repetitions of concentric-concentric contractions will be completed. Three submaximal contractions will be allowed prior to three maximal contractions to allow for familiarization with the procedure. Isokinetic dynamometer results have previously been shown to produce reliable measurements for isokinetic strength[60, 61]. For ankle testing measurements, subjects will be placed in a semi recumbent position with 60° of knee flexion. Strength measurements will be made at 30°/s. For knee flexion/extension isokinetic strength, subjects will be placed in an upright seated position with knees and hips flexed to 90°[62]. Strength measurements will be made at 60°/s. For hip ab/adduction isokinetic strength, subjects will be standing in a vertical position and measurements will be made at 30°/s. Consistent verbal encouragement will be given in order to promote maximal effort.

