### Kinematics and kinetics

To assess lower extremity running mechanics, subjects will perform 20 over-ground running trials (3.5 m/s ± 15%). Additionally, subjects will perform five minutes of treadmill running at their preferred speed following a five minute walking warm up at 2.5 mph. For the over ground running trials, kinematic data will be collected using an eight high-speed video camera system (Motion Analysis Corporation, Santa Rosa, CA, USA) at a sampling rate of 240 Hz. Previous studies have found that motion capture systems provide results with clinically acceptable errors and relatively high reliability depending on the accuracy of marker placement[68]. Three-dimensional marker traces will be reconstructed using Expert Vision Three-Dimensional Analysis software (Motion Analysis Corporation, Santa Rosa, CA, USA). Kinetic data will be collected simultaneously using a force plate (Kistler Instruments AG, Winterthur, Switzerland) embedded within the laboratory floor with a sampling frequency of 2400 Hz. Retro-reflective markers will be mounted on the rearfoot, shank, and thigh of the right lower extremity and the pelvis to measure three dimensional movements of the ankle, knee, and hip joints[69]. Markers will be placed over the right greater trochanter, medial and lateral knee joint axis, and medial and lateral malleoli in order to define joint centers. Position data from a static neutral trial will be collected in order to define the segment coordinate system. Joint markers will be removed for the running trials. For the treadmill walking, 26 retro-reflective markers were skin-mounted the arms, torso, pelvis, legs and feet. Markers were placed on both sides of the body (three on each foot, three on each shank, three on each thigh, one on each greater trochanter and lateral knee joint center, four on the pelvis) as well as two on the sternum, one on the spine (C7), and one on each shoulder. All biomechanical testing sessions will be completed by the same researcher in order to ensure maximum reliability.

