#### Analysis

Descriptive statistics of baseline characteristics of the participants in each group will be reported (mean, standard deviation, 95% confidence intervals). These will be presented in tabular form in order to determine if the groups were well balanced with respect to age, mass, height, weekly mileage and running experience[76].

For the isokinetic strength measurements, the peak torque of the three maximal isokinetic contractions will be identified. For postural control, the average entropic half-life in the medio-lateral and anterior-posterior direction will be calculated for the eyes open and eyes closed single limb tasks in the ML and AP direction. Additionally, the average COP 95% ellipse area, average COP path length, and average SEBT reach distance will be calculated. For the over ground running trials, a discrete analysis will be completed using Kintrak software (Human Performance Laboratory, Calgary, Canada) to calculate three-dimensional joint angular displacements, and moments for the ankle, knee and hip joints. Specifically, peak ankle eversion/inversion angle and moment, peak knee ab/adduction angle and moment, peak knee internal/external rotation angle and moment, peak hip ab/adduction angle and moment and peak hip internal/external rotation angle and moment during the stance phase will be calculated. All variables will be normalized to the stance phase of the right foot where heel contact and toe off will be identified as crossing a 15 N threshold. Additionally, a vector-based analysis approach (iterative support vector machine [SVM]) will be used to determine the classification rate of subjects following training as well as to identify the movements that have changed following training using the entire data set rather than discrete time points for the treadmill run[77]. A multivariate linear regression will be used to determine whether the change from baseline to the end of training in each variable for each training group is significantly different from the change found in the control group while controlling for age, gender, and any other baseline differences between the groups.

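### As written, the allocation envelope may be opened at consent, before baseline testing, so effort-dependent baselines in a non-blinded change-score trial may be measured with the group known

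*Protocol article*

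**What the plan says.** All places are in the protocol article.

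- **Randomization procedure.** Allocation follows consent: "Once potential subjects have provided written, informed consent, they will sequentially draw an envelope". Subjects then "write their details on that envelope before opening to determine their group allocation". No other step is named between consent and opening. The single block of 120 is justified as avoiding "predictable random assignments using smaller block sizes in a non-blinded study design", so the trial is openly described as non-blinded.
- **Measurements.** "Subjects will attend one testing session prior to the training intervention and one testing session immediately following the training intervention". The first session is placed relative to training, not relative to the envelope.
- **Isokinetic strength.** Torque comes from maximal voluntary contractions: "Consistent verbal encouragement will be given in order to promote maximal effort".
- **Kinematics and kinetics.** "All biomechanical testing sessions will be completed by the same researcher in order to ensure maximum reliability". No masking of this researcher is stated.
- **Analysis.** The regression asks "whether the change from baseline to the end of training in each variable for each training group is significantly different" from the change in the control group, adjusting for age, gender and other baseline imbalances. Injury is analysed separately, as a rate, by Poisson regression.
- **Study design.** The section refers the reader to Figure 1 for the study flow; that figure is not available here.

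**The concern.** In an exercise trial the runner cannot be kept unaware of the group during training or at post-test. Baseline is the one measurement that can be fully protected, simply by taking it before the envelope is opened. The text does not secure this.

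If the group is known at baseline, a runner may try more or less hard, or a tester who knows the group may encourage differently. Because the outcome is post-test minus baseline, a depressed baseline in one arm appears as a gain in that arm, and an inflated one as a loss.

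Two further consequences follow from the same ordering. A runner who opens the envelope and leaves before the first session contributes no change score, and such departures may depend on the group drawn. Also, the Target population section counts the injury-free period back from testing rather than from consent, so if testing follows opening, part of eligibility could be settled after allocation is known.

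**Working it through.** **1. The order of events.** Two sequences satisfy both sections:

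- consent, envelope opened, baseline session, training;
- consent, baseline session, envelope opened, training.

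The first is the more literal reading, since consent is the only trigger named. Nothing in the text excludes the second. So the text permits opening before baseline but does not require it.

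**2. Which outcomes are exposed.**

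- Isokinetic torque: maximal and encouraged, so strongly effort-dependent.
- SEBT reach: volitional, so exposed.
- Single-leg stance (path length, 95% ellipse area): plausibly exposed through concentration and effort.
- Over-ground running mechanics: 20 trials in a fixed band of 3.5 m/s ± 15%, so little exposed.
- Injury: a rate, with no baseline value to distort.

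**3. The plan's own figures.** Inputs from the Sample size section: effect size 0.71, α = 0.05 (taken as two-sided), power 80%, dropout 20%.

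- n per group = 2(1.960 + 0.842)² / 0.71² = 31.14, rounded up to 32.
- Recruitment = 32 / (1 − 0.20) = 40.

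Both stated figures reproduce, and this point changes neither.

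**4. Illustration of size.** The documents give no bias, so the shift is assumed. Let b be the between-arm difference in baseline distortion, in SDs of the change score. It passes one-for-one into the difference in mean change. With 32 per group the standard error is √(2/32) = 0.25, and with no true effect

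rejection rate = 1 − Φ(1.96 − b/0.25) + Φ(−1.96 − b/0.25).

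| b (assumed) | b/0.25 | Two-sided rejection rate |
|---|---|---|
| 0 | 0 | 5.0% |
| 0.1 | 0.4 | 6.9% |
| 0.2 | 0.8 | 12.6% |
| 0.3 | 1.2 | 22.4% |
| 0.5 | 2.0 | 51.6% |

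These are normal approximations for one comparison. The rate is the same whichever arm is distorted.

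**5. Does the planned adjustment repair it?** Suppose the baseline value of the outcome is among the covariates, which the text does not say. With no true effect and a baseline distorted by δ in one arm, the unadjusted change comparison is off by δ in absolute size. The adjusted comparison is off by βδ, where β is the within-arm slope of post-test on baseline. With β between 0 and 1 the bias shrinks, but it vanishes only at β = 0.

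**The case against.** The strongest reply is that no sentence says the envelope is opened before baseline. Consent can be read as a precondition for the draw rather than as its moment, and Figure 1 may put baseline testing first. An article may also leave step order to the full protocol. This stands as far as it goes: the point cannot be put as a stated fact, only as something the text allows. It does not remove the point, because the article does describe the trigger for allocation, and that trigger offers the baseline no protection.

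Other parts of the reply also stand:

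- **The tester's knowledge is not established.** Subjects open the envelopes themselves, and the article does not say whether the tester is also the study coordinator who hands out the exercises. Consistent encouragement is specified, which is some standardisation.
- **A reader might infer that every change score is affected.** The documents do not support this. Over-ground running is speed-controlled and not a maximal test, and injury is not a change score.
- **A reader might infer that the bias favours the trial's hypotheses.** The documents do not show this either. Disappointed controls could hold back at baseline, which works against the training arms. The Hypotheses section also predicts no knee or hip strength gain from ankle strengthening, so a general baseline under-effort in that arm would contradict the prediction.
- **Withdrawal between opening and baseline is a possibility, not an observed fact.** The control arm has an activity-matched routine, and 20% dropout is planned for. That allowance protects the numbers, however, not the comparability of those who remain.

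**Conclusion.** The point holds in a limited form. The text allows allocation to be known to the runner, and possibly to the tester, when baseline is measured. In a non-blinded trial analysed on change from baseline, this can bias isokinetic torque and SEBT reach, and possibly single-leg stance.

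Neither direction nor size can be taken from the documents. The false-positive rates above rest on assumed shifts, a normal approximation, 32 analysed per group and no true effect; they show sensitivity and are not an estimate. Expressing such a shift in torque as a share of the planning effect of 0.71 would not be valid, because that effect concerns change in the centre-of-pressure ellipse area.

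A reader might also conclude that no analysis could remove the bias. That is too strong: a comparison of post-test values alone would avoid the baseline distortion, but it is not what is planned. The planned regression would not reliably remove it.

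If Figure 1 places baseline first, what remains is a wording problem: the randomization text must be brought into line with it.

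**What to change.** In the Randomization procedure section, replace consent as the sole trigger with a statement that the envelope is drawn and opened only after consent is given, eligibility is confirmed and the full baseline session is complete. If Figure 1 shows another order, reconcile the two. This reorders two enrolment steps; the envelopes, the allocation list and the sample size are unchanged.

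As a separate, low-cost step, ask runners not to reveal their group to the tester at post-test, and give the physiotherapist and those processing data coded IDs without group labels. This does not address baseline timing, but it limits the same kind of bias later in the trial. The cost is some extra data handling, and the masking will be imperfect because runners may disclose their group.

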### Treatment arms

A home-based warm up routine consisting of aerobic activity, static stretching and dynamic stretching will be taught with recommended adherence by all three groups five times a week[41] The control group subjects will be asked to complete this warm up for twenty five minutes with no additional training (Table 1). The strength group and the balance group will be asked to complete specific training program components for 20 minutes in addition to a 5-minute warm up. The strength group will complete a training program using Thera-Band elastic bands[55] (Figure 2). The balance group will have training incorporating a Both Sides Up (BOSU) device with activities increasing in difficulty every two weeks[43, 46, 56] (Table 2). Subjects will meet in person with the study coordinator every two weeks to receive their new training exercises. All subjects will be asked to complete their respective routines five sessions per week. If the subject plans to run that day, they will be asked to complete their training immediately before their running session. If the subject does not plan to run that day, they are able to complete their respective training whatever time of day is convenient. Subjects will be asked to complete a physical activity log documenting the number of minutes completed for each exercise in their training routine as well as the number of minutes of running exposure on a weekly basis[42]. It is hypothesized that the common warm up will have no effect on muscular strength, lower extremity running mechanics, postural control, or injury prevention.

**Table 1 Tab1:** **Twenty-five minute warm up routine for the activity matched control group**

Category	Movement	Duration
Aerobic	Side-to-side shuttle, high knee skipping, light running	5 min
Static stretch	groin, hamstrings, quadriceps, calves (30 seconds each)	10 min
Dynamic stretch	Buttock Kicks – 4 minutes	10 min
	Leg Swings – Side, 3 minutes	
	Leg Swings – Front, 3 minutes	
	Total Time	25 min

**Figure 2 Fig2:**
[figure not shown]
**Twenty-five minute training routine for the isolated ankle strengthening group.**

**Table 2 Tab2:** **Twenty-five minute training routine for the functional balance training group**

Category		Movement				Duration	
Aerobic		Side-to-side shuttle, high knee skipping, light running				1 min	
Static stretch		groin, hamstrings, quadriceps, calves (30 seconds each)				2 min	
Dynamic stretch		Buttock Kicks – 1 minutes				2 min	
		Leg Swings – Side, 30 seconds					
		Leg Swings – Front, 30 seconds					
		Total time				5 min	
Balance weeks 1,2		Balance weeks 3,4		Balance weeks 5,6		Balance weeks 7,8	
Movement	Reps	Movement	Reps	Movement	Reps	Movement	Reps
Lunges: forward and backward	10 per side	Lunges: round the clock	5 per side	Lunge forward onto BOSU ball and backwards off of BOSU ball	10 per side per condition	Lunge forward onto BOSU ball and backwards off of BOSU ball	20 per side per direction
Squat: bipedal, box touch	10	Squat: bipedal on BOSU, ball facing down	10	Squat: single leg	10 per side	Squat: single leg mini squat on BOSU ball, ball facing up	10 per side
Hop in a box formation: bipedal	5 per direction	Hop in a box formation: single leg	3 per side per direction [6 per side in total]	Hop onto BOSU: Bipedal, ball facing upwards	10	Hop onto BOSU: single leg, ball facing upwards, forward, and side	5 per side per direction
Single leg stance: eyes open, eyes closed, variations with lower limb movements for increasing difficulty	5 per visual condition, 30 sec	Single leg stance: eyes open, eyes closed, variations with lower limb and trunk movements for increasing difficulty	5 per visual condition, 30 sec	Single leg stance on BOSU: ball facing upwards	5 per visual condition, 30 sec	Single leg stance on BOSU: ball facing upwards, variations in arm and torso movements.	5 per visual condition, 30 sec
Lateral Jump: left to right side	20 per side	Star Jump: left to right side	5 per side	Star jump: right leg to right leg, left leg to left leg	3 per side	Star jump: right leg to right leg, left leg to left leg, increasing jumping distance	3 per side

#### Measurements

Baseline characteristics will be collected for each subject including height, mass, running frequency, running experience, and injury history. Subjects will attend one testing session prior to the training intervention and one testing session immediately following the training intervention (within 9 weeks from baseline) for biomechanical data collection. These testing sessions will involve the collection of isokinetic strength data and the collection of lower extremity running mechanics (kinematics and kinetics) and postural control (dependent variables). Postural control will be assessed as balance deficits have previously been shown to be predictive of future ankle sprains in healthy athletes[57–59].

### Isokinetic strength

As running is dynamic, isokinetic measurements of strength will be completed. Isokinetic strength will be measured using a Biodex System 3 dynamometer (Biodex Medical System Inc, New York, NY, USA) to assess average peak torque for ankle eversion/inversion strength, ankle plantar flexion/dorsiflexion strength, knee flexion/extension strength and hip ab/adduction strength. For each movement, three maximal repetitions of concentric-concentric contractions will be completed. Three submaximal contractions will be allowed prior to three maximal contractions to allow for familiarization with the procedure. Isokinetic dynamometer results have previously been shown to produce reliable measurements for isokinetic strength[60, 61]. For ankle testing measurements, subjects will be placed in a semi recumbent position with 60° of knee flexion. Strength measurements will be made at 30°/s. For knee flexion/extension isokinetic strength, subjects will be placed in an upright seated position with knees and hips flexed to 90°[62]. Strength measurements will be made at 60°/s. For hip ab/adduction isokinetic strength, subjects will be standing in a vertical position and measurements will be made at 30°/s. Consistent verbal encouragement will be given in order to promote maximal effort.

